## Abstract

**Background:**

Practitioners of traditional Chinese medicine know that auricular point acupressure (APP) using vaccaria seeds on the large intestine point (CO7) has a significant effect on postoperative gastrointestinal dysfunction. A standardized, clinical, research design will transform this clinical experience into scientific evidence, thus providing a basis to promote the wider use of this therapy. We aim to carry out a double-blind, randomized, controlled trial (RCT) to evaluate the efficacy and safety of APP treatment for gastrointestinal dysfunction after laparoscopic cholecystectomy.

**Methods/design:**

This study is a randomized, double-blind, controlled, single-center, clinical, pilot trial. It has been designed according to the Consolidated Standards of Reporting Trials (CONSORT 2010) guidelines as well as the Standards for Reporting Interventions in Controlled Trials of Acupuncture (STRICTA). Study subjects are being selected from among hospitalized patients who have undergone laparoscopic cholecystectomy at the Department of Minimally Invasive Surgery of Tianjin Nankai Hospital. Qualified subjects will be assigned randomly either to the APP group or to the APP sham stimulation group on the basis of random numbers generated using SPSS 19.0. A specifically appointed investigator will be responsible for the randomization. The APP therapy (or sham stimulation) will be performed 6 h after surgery and every 12 h subsequently; six sessions will be conducted, each lasting 3 min. The first evaluation will be performed immediately before the first treatment (6 h after surgery) and, then, every 12 h for seven evaluations. The primary outcome is the time to first passage of flatus after surgery; the secondary outcome measures are abdominal distension, nausea, vomiting, time to first defecation, psychological status, and quality of life.

**Discussion:**

This pilot trial is a standardized, scientific, clinical trial designed to evaluate the efficacy and safety of APP treatment—using vaccaria seeds on CO7—for gastrointestinal dysfunction after laparoscopic cholecystectomy. We aim to provide objective evidence to promote this therapy in clinical practice.

**Trial registration:**

Chinese Clinical Trial Registry, ChiCTR-IPR-15007643. Registered on 14 December 2015.

**Electronic supplementary material:**

The online version of this article (doi:10.1186/s13063-016-1404-3) contains supplementary material, which is available to authorized users.

## Background

Gastrointestinal dysfunction is a common complication of abdominal surgery; its main symptoms include delayed flatus and defecation, abdominal distention, abdominal pain, nausea, and vomiting. Therefore, promoting rapid recovery from gastrointestinal function has become integral to postoperative rehabilitation [1]. Gastric motility typically recovers within 24–48 h after surgery, whereas colonic motility is generally restored within 48–72 h [2]. Thus, it often takes 2–3 days for the patient to recover from gastrointestinal dysfunction. Postoperative gastrointestinal dysfunction is usually treated using alvimopan; however, this drug has adverse effects such as nausea and vomiting [3].

Auricular point acupressure (APP) may be a noninvasive physical treatment for the condition of postoperative gastronintestinal dysfunction [4, 5]. This therapy involves stimulating sensitive points on the auricle using vaccaria seeds; the points correspond to specific organs. In previous studies, we compared subjects’ postoperative time to flatus between an experimental group that received APP using vaccaria seeds on the large intestine point (CO7; 20.19 ± 3.14) and a control group that received APP sham stimulation (30.82 ± 5.58). Preliminary results showed that the APP using vaccaria seeds on CO7 can promote the recovery of gastrointestinal motility after abdominal surgery.

## Methods/design

### Design

This study is a randomized, double-blind, controlled, single-center, clinical, pilot trial (Fig. 1), which was designed in accordance with the Consolidated Standards of Reporting Trials (CONSORT 2010) guidelines as well as the Standards for Reporting Interventions in Controlled Trials of Acupuncture (STRICTA) [6]. As the Standard Protocol Items: Recommendations for Interventional Trials (SPIRIT) checklist shows in Additional file 1, we are selecting in-patients who have undergone laparoscopic cholecystectomy (LC) between January 2016 and June 2016 at the Department of Minimally Invasive Surgery of Tianjin Nankai Hospital. The APP will be performed by specialist nurses who have more than 5 years of experience and have held intermediate professional titles.

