### Blinding methods

We will ensure that the evaluators of treatment efficacy are unaware of the group assignments of the subjects by (1) blinding the subject data and (2) using independent statisticians. Moreover, the data will be analyzed by statisticians who are unaware of the group assignment. Thus, operators, evaluators, data administrators, and statisticians will work independently in this study.

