### Experimental group

Pressure will be applied to both ears alternately without rubbing (to avoid skin damage and infection at the acupuncture point). Optimal pressure will be considered to have been achieved when the subject feels localized tingling pain; the vaccaria seeds will then be fixed to prevent them from coming loose. We use small adhesive tape with spherical vaccaria seeds to adhere to the auricular points, and then, we press the points with digital pressure for 10 s. A 3-s pause occurs between each two pressings. After every intervention, we will remove the tapes. We will use the Visual Analog Scale (VAS; Fig. 3) to evaluate pressure intensity [9]. In accordance with preliminary experiments, the pressure intensity will be controlled at 50 mm. Because the pre-operative fasting time is relatively long, and stimulation of acupuncture points can lead to reduced blood sugar levels, it is necessary to observe whether the subject displays symptoms such as paleness and apathy during the treatment. If such symptoms appear, then the procedure will be ceased immediately, a blood sugar test will be performed, and treatment will be administered as necessary.

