### Control group

The subjects in the control group will receive sham APP, i.e., vaccaria-seed tapes adhered to the auricular points with no added pressure. Furthermore, to ensure ethical care and better communication with subjects in the control group, the subjects will be given health education (disease awareness, dietary guidance, exercise, and psychological care) during the treatment.

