### Outcome measures and participant timeline

#### Outcome measures

Baseline dataDemographic data will be recorded using a general information questionnaire, which we designed in house. The questionnaire includes questions on age, gender, education, occupation, weight, and height.Clinical characteristics will be recorded using another in-house-designed questionnaire. Specifically, data will be collected on the surgery time, anesthesia time, intraoperative blood loss, intraoperative fluid transfusion volume, and vital signs (temperature, heart rate, respiratory rate, and blood pressure).Primary outcome measureThe primary outcome is the time to first passage of flatus—we will begin observing and recording when subjects return safely to the ward, and the subjects and their families will be asked to record the time of the first passage of flatus. The interval between the two time points will be then calculated.Secondary outcome measuresTime to first defecation: We will observe and record when the subjects return safely to the ward, and the subjects and their families will be asked to record the time of first defecation. The interval between the two time points will then be calculated.Abdominal pain: The subjects’ degree of postoperative pain will be assessed using the VAS scale [10]. The first evaluation will be performed 6 h after surgery, immediately before the first treatment. Evaluations will then be carried out once every 12 h, for seven evaluations. Assistance will be given to subjects and their families in recording this information.Abdominal distention: The Likert scale will be used to assess the subjects’ degree of postoperative abdominal distention [11]. The first evaluation will be performed 6 h after the surgery, immediately before the first treatment. Evaluations will then be carried out once every 12 h, for seven evaluations. Assistance will be given to subjects and their families in recording this data.Nausea: The VAS scale will be used to assess subjects’ degree of postoperative nausea [10]. The first evaluation will be performed 6 h after the surgery, immediately before the first treatment. Evaluations will then be carried out once every 12 h, for seven evaluations. Assistance will be given to subjects and their families in recording this data.Vomiting: The frequency of postoperative vomiting will be recorded. The first evaluation will be performed 6 h after the surgery, immediately before the first treatment. Evaluations will then be carried out once every 12 h, for seven evaluations. Assistance will be given to subjects and their families in recording this data.Mental status: The Hospital Anxiety and Depression Scale (HADS) will be used to assess the subjects’ postoperative mental status [12]. The HADS consists of 14 items: seven assess depression, and the other seven assess anxiety. The scores of the anxiety and depression subscales are classified as follows: 0–7 points indicate no symptoms, 8–10 points indicate suspected symptoms, and 11–21 points indicate confirmed symptoms. The first evaluation will be performed 24 h before surgery, and the second evaluation will be performed on the day of discharge.Quality of life: the Gastrointestinal Quality of Life Index (GIQLI) will be used in this study [13]. The GIQLI aims to measure the quality of life of subjects with digestive diseases and includes five domains: subjective symptoms, physiological functional status, daily life, social activities, and psychological and emotional state. Within these domains, 36 items are assessed, each with a score from 0 to 4 points, for a total possible score of 144 points. The normal population will score 12–125 points. The first evaluation will be performed 24 h before surgery, and the second will be conducted 2 weeks after discharge. A follow-up evaluation will be carried out 1 month after discharge. Higher scores indicate better health status.Safety indicatorsAn event can be defined as an adverse event if at least four subjects suffer a symptom—such as local skin allergies, dizziness, and low blood sugar—during the treatment-evaluation period. These events will be statistically analyzed, and treatment safety is evaluated on this basis, in accordance with the research protocol. If serious adverse events occur, they will be immediately reported and managed accordingly.Participant timelineFor a complete overview of the time schedule of enrollment, interventions, and assessment for participants, see Fig. 4.

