### Quality control

To ensure the quality of this research, this pilot trial has undergone multiple modifications and revisions by relevant digestive disease specialists, acupuncture experts, professional statisticians, and research methodologists. Strict inclusion and exclusion criteria have been established. To maintain data objectivity, we will ensure that the statisticians and evaluators were blinded. All researchers, and particularly APP operators, have completed our training, thereby ensuring consistent treatment practices and uniformity in the terminology used for communication with the subjects. All operators have a diploma in Chinese Medicine, and they were trained uniformly—before subject recruitment—to pass a test based on the operational protocol. The drugs and materials used in this research have been purchased uniformly; thus, we can ensure that our conclusions will be reliable. The CRF is filled in strictly and in accordance with the CRF instructions; in addition, detailed data regarding subject observations are being recorded. We require the researchers to be conscientious and thorough during data entry, and a corresponding evaluation report is attached. Original data cannot be altered; if modifications are made, these will be explained in detail and accompanied by the signature of the staff member who made the change.

This study involves a two-level quality inspection system. Level 1 involves a quality control inspection. Quality inspectors will be appointed by the study leader; they will design a quality checklist and monitor the records of all original data, data reports, and adverse events in accordance with that checklist. Level 2 involves quality supervision. The quality supervisor will be appointed directly by the study leader. The supervisor will (1) monitor the research operators’ command of the research design and process; (2) confirm the authenticity, accuracy, and integrity of all research data records, reports, and CRF; and (3) ensure consistency in the original data.

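### The trial is labelled double-blind, but only evaluators and statisticians are said to be blinded, operators must know the arm, and subjects and families record the primary endpoint.

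*Protocol article*

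**What the plan says.** The Abstract and the Design section both call the trial double-blind; the latter reads "This study is a randomized, double-blind, controlled, single-center, clinical, pilot trial".

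The sections that spell this out name two roles. Under Blinding methods: "We will ensure that the evaluators of treatment efficacy are unaware of the group assignments of the subjects", and "the data will be analyzed by statisticians who are unaware of the group assignment". Under Quality control: "we will ensure that the statisticians and evaluators were blinded". Randomization adds that recruiters and evaluators do not know the allocation sequence. For operators the article claims only independence: "operators, evaluators, data administrators, and statisticians will work independently in this study".

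The two procedures differ in what the subject feels. In the experimental group, "Optimal pressure will be considered to have been achieved when the subject feels localized tingling pain", with intensity held at 50 mm on a VAS. The controls receive "vaccaria-seed tapes adhered to the auricular points with no added pressure". Health education is described under Control group only.

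For the primary endpoint, "the subjects and their families will be asked to record the time of the first passage of flatus". Time to first defecation is collected in the same way.

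**The concern.** A reader who sees double-blind will normally take it that participants, and often those giving treatment, do not know the allocation. Here the people who deliver the treatment must know it. The people who supply the primary endpoint are never said to be unaware of it.

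The primary endpoint is a time noted by the subject or family and compared by a two-sample t test. Any influence of perceived allocation on when an event is noticed or written down enters the comparison directly, and blinding the evaluator or statistician afterwards cannot remove it. Pain, nausea, distention, HADS and GIQLI are also reported by the subject. The label therefore promises more protection than the described procedures give, and it bears on how far an effect of acupressure can be separated from expectation and reporting.

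**Working it through.** **1. Who is blinded, by role**

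| Role | What the article says | Reading |
|---|---|---|
| Evaluators | Unaware of assignment (Blinding methods, Quality control) | Claimed; but Randomization puts the two arms in separate wards, so an evaluator who knows the ward scheme could infer the arm |
| Statisticians | Unaware of assignment (same sections) | Claimed |
| Recruiters | Do not know the sequence (Randomization) | Allocation concealment |
| Operators | Work independently | Not blinded: they either press to tingling or do not |
| Participants and families | No statement | Open; partial protection at best |

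**2. Who supplies the primary endpoint.** Subjects and families (Outcome measures), the row for which no blinding is stated.

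**3. The plan's own sample size.** Inputs from Sample size estimation: SDs 3.14 h and 5.58 h, difference 4 h, Z values 1.96 and 0.84.

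- Sum of variances: 3.14² + 5.58² = 9.8596 + 31.1364 = 40.996.
- n = (1.96 + 0.84)² × 40.996 / 4² = 7.84 × 40.996 / 16 = 20.09, rounded up to 21 per group.
- With 15% dropout: 21 / 0.85 = 24.7, so 25 per group and 50 in total.

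This reproduces the stated figures. The sample size is not in dispute.

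**4. Illustration of what a reporting shift would do.** Assume no true effect and a systematic shift b, in hours, in the recorded time between arms. The documents give no value for b; the range 0 to 3 h is assumed. For the planned two-sided t test at 0.05:

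- SE = √(40.996 / n): 1.40 h at 21 per arm, 1.28 h at 25 per arm.
- Rejection probability = P(|T| > critical value), where T is noncentral t with 2n − 2 degrees of freedom and noncentrality b / SE.

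| Assumed shift b | 21 per arm | 25 per arm |
|---|---|---|
| 0 h | 5.0% | 5.0% |
| 0.5 h | 6.4% | 6.7% |
| 1 h | 10.8% | 11.9% |
| 2 h | 28.7% | 33.4% |
| 3 h | 55.4% | 63.1% |

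The 21 column is the planned evaluable number; the 25 column assumes no dropout. Shifts of 1 h and 2 h are 25% and 50% of the 4 h target difference.

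**The case against.** The best defence is that feeling a procedure is not the same as knowing the allocation. Inclusion criteria require subjects with no earlier experience of the therapy. The wards are separated so that the arms do not talk to each other. Both arms get the same seed tapes, and operators are trained to use uniform terms with subjects. Someone who never sees the other procedure may not know that tingling marks the active one. What subjects are told is decisive, and the consent wording is not shown. This stands. A reader might infer that participants cannot be blinded and that the person recording the primary endpoint is certainly unblinded; the documents do not support going that far.

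It can also be said that staff observe and record from the return to the ward, that flatus can hardly be learned except from the patient, and that a clock time is less open to expectation than a rating. These points are fair. Collecting the time this way is not in itself an error; the difficulty is the label placed over it.

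The error rates rest on an assumed shift, and nothing in the documents shows that one exists or in which direction. That stands too.

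Finally, an article condenses a longer protocol, which might contain a blinding check. The absence of such a check is therefore not the point. The article has a dedicated blinding section that says who is blinded, and that list does not match the label.

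**Conclusion.** The point holds as an unsupported design label. Operator unblinding follows directly from the two described procedures. Participant blinding is neither stated nor assured: there is partial protection, set against an unmatched sensation and education described for one arm only. Evaluator blinding does not reach the primary endpoint or time to first defecation, because subjects and families record both.

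The size of any bias cannot be derived from the documents. Conditional on a 1 h shift with no true effect, the nominal 5% error becomes about 11–12%; on a 2 h shift, about 29–33%. A reader might take these as the trial's actual error rates. They are not; they show only how sensitive the planned test is to an assumed shift. No sample-size figure changes.

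**What to change.** 1. Replace the double-blind label in the Abstract and Design with a statement by role: sham-controlled, evaluators and statisticians blinded, operators not blinded, participant blinding not assured. Limit the conclusions on the self-recorded primary outcome and the self-reported secondary outcomes to match.

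2. Reconcile the claim of evaluator blinding with housing the arms in separate wards, by stating how an evaluator at the bedside is kept from inferring the arm. Without this, the revised label is itself open to doubt.

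3. Add one allocation-guess question, reported by arm, only after the final session and the final inpatient evaluation. Asked after the first session, about 6 h after surgery, it would usually come before first flatus (preliminary means 20.19 and 30.82, from Background) and could prompt subjects to speculate about their arm.

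Having the evaluator log flatus times at the 12-hourly evaluations would not solve the problem, since it only transcribes the patient's report.

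The cost is a less favourable label and one extra item on the case report form. The GIQLI assessments after discharge would still follow the guess question, which is a small residual drawback. Recruitment is ongoing, so the answers can be collected only from subjects who have not yet passed that point. Treatment and sample size are unchanged.

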**Fig. 1 Fig1:**
[figure not shown]
Flow chart of the study

Patients will be randomly assigned either to the APP group or to the APP sham stimulation group on the basis of numbers randomly generated using SPSS 19.0. A specifically appointed investigator will be responsible for the randomization. The APP (or sham stimulation) will be performed 6 h after surgery and every 12 h subsequently; six sessions will be conducted, each lasting 3 min. The first evaluation will be performed immediately before the first APP session (6 h after surgery), and then every 12 h for seven evaluations.

### Study subjects

According to the data from the preliminary study, and given that the primary outcome is the time to the first passage of flatus, the estimated sample size of this study should be 50 cases, with an α value of 0.05, a power of 80 %, and a 15 % dropout rate.

In order to ensure the accuracy of the results, the following inclusion and exclusion criteria have been established.

#### Inclusion criteria

Subjects who are being enrolled in this clinical trial (1) must be age 18 to 65 years; (2) fulfill the classification criteria of the American Society of Anesthesiologists I − II and be scheduled to undergo LC under general anesthesia [7]; (3) have no experience of APP before this study; (4) are not involved in any other clinical trials during the same period; and (5) do not have cognitive impairment, aphasia, or mental disorders, thereby possessing unimpaired communication ability, and can understand and sign the informed consent form.

#### Exclusion criteria

Subjects are excluded if they (1) are pregnant or lactating; (2) have a history of abdominal surgery; (3) have undergone more procedures than LC alone as part of their treatment; (4) have sustained damage to the selected acupressure point or have an allergy to the adhesive; (5) suffer from severe gastrointestinal or chronic pain disorders (such as chronic pelvic pain), and have taken analgesic drugs during the past 48 h—or over a long period of time; (6) have a serious disease of the heart, brain, liver, kidney, or hematopoietic system; or (7) have a history of drug abuse (e.g., morphine), motor-induced or surgery-induced vomiting, obesity (body weight > 80 kg), diabetes, or are bedridden.

#### Elimination criteria

Subjects will be removed from the study if they (1) switch to laparotomy; (2) refuse to continue this treatment after inclusion, regardless of the reason; (3) experience serious complications during treatment (e.g., peritonitis or biliary fistula); (4) are transferred for other specialist treatment, became comatose, or die; (5) cannot attend follow-up visits, for whatever reason; (6) do not meet the inclusion criteria but were included by mistake; or (7) show poor clinical compliance (failure to adhere to the treatment protocol or to provide complete information), which may have affected the efficacy and safety of the treatment.

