#### Statistical analysis

Content of statistical analysisSample distribution: The absolute number of dropouts as well as the rate will be described for each data set. These data will be analyzed, and the reasons for each termination are listed in detail.Balance comparison: The subjects’ general information will be compared to assess the comparability of the two groups.Efficacy analysis: The subjects’ time to first passage of flatus will be used as the primary outcome measure to evaluate the efficacy and safety of APP in treating gastrointestinal dysfunction after laparoscopic cholecystectomy. The means and standard deviations will be calculated to describe the outcome measure, and the experimental and control groups will be statistically compared using two independent-sample *t* tests. The subjects’ time to first defecation, abdominal pain, abdominal distention, nausea, vomiting, mental status, and quality of life—i.e., the seven secondary outcome measures—will be used to evaluate the efficacy of the APP. Six of these—namely, the time to first defecation, abdominal pain, abdominal distention, nausea, vomiting, and quality of life—will be described using mean ± standard deviation. The scores for mental status will be recorded and categorized in terms of the classification criteria. The statistical analysis of time to first defecation is the same as that of time to first passage of flatus; abdominal pain, abdominal distention, nausea, vomiting, and quality of life will be statistically compared between groups using Repeated Measures Analysis of Variance (RMANOVA). However, before the RMANOVA is performed, a sphericity test will be used to determine whether the data are suitable for analysis using RMANOVA. If the data do not meet the conditions of sphericity, the correction factor *ε* will be used to correct the degree of freedom before the RMANOVA is performed. The categorical measure of mental status will be analyzed using either the rank-sum test or Spearman’s rank correlation.Safety analysis: In accordance with the above definitions of adverse events, we compiled a list describing, grading, and explaining the adverse events in detail. We will ascertain descriptive statistics of the absolute number—as well as the incidence—of each adverse event in both groups. When making comparisons, we will use the *χ*^2^ test or Fisher’s exact test for statistical analysis.Methods of statistical analysisData will be analyzed in accordance with the principle of intention-to-treat (ITT). That is, we will include all subjects who were treated at least once in the trial. Efficacy and safety measures will be analyzed in accordance with “per-protocol” (PP), whereby we will include all subjects who completed the entire trial and followed the protocol requirements. Quantitative variables in the trial data will be expressed as $$ \overline{\mathrm{X}}\pm \mathrm{S}\mathrm{D} $$ for statistical description, whereas qualitative variables will be recorded as the number of cases in each category. If the quantitative variables constitute repeated measures data, then RMANOVA will be used for comparison, and the sphericity test will be used to determine the suitability of, as well as to correct, the data. Qualitative variables will be analyzed using either the rank-sum test or Spearman’s rank correlation; count data for incidence will be compared using the *χ*^2^ test or Fisher’s exact test. All statistical tests are two-sided, and differences with *P* values < 0.05 will be considered statistically significant. Statistical analysis will be performed using SPSS 19.0 statistical software for calculations.

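### Subjects who stop treatment are removed from the study with no provision for further assessment, which conflicts with an intention-to-treat set of everyone treated at least once

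*Protocol article*

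**What the plan says.** Elimination criteria lists seven grounds for removal. It begins: "Subjects will be removed from the study if they (1) switch to laparotomy; (2) refuse to continue this treatment after inclusion, regardless of the reason". Item (5) removes subjects who "cannot attend follow-up visits, for whatever reason". Item (7) removes subjects for poor compliance that may have affected efficacy and safety. The article does not distinguish stopping acupressure from leaving the study, and it does not say that assessments continue after a subject stops.

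Statistical analysis states the ITT principle and explains it: "we will include all subjects who were treated at least once in the trial". The next sentence says "Efficacy and safety measures will be analyzed in accordance with" a per-protocol principle, under which "we will include all subjects who completed the entire trial and followed the protocol requirements". On losses, it says "The absolute number of dropouts as well as the rate will be described for each data set", with reasons for termination to be listed.

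**The concern.** The trigger in item (2) is stopping treatment, but the consequence is leaving the study. The words "refuse to continue this treatment after inclusion, regardless of the reason" do not limit the rule to withdrawn consent. An analysis of everyone treated at least once needs outcomes from people who stop, and this rule takes those people out.

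At stake are the primary outcome for subjects who stop before passing flatus, the remaining 12-hourly evaluations, the HADS at discharge and the GIQLI at 2 weeks and 1 month after discharge. An analysis plan cannot repair this later, because a flatus time not recorded on the ward cannot be recovered. Item (5) adds a case of its own: a subject with a complete hospital record, flatus time included, is removed for being unable to attend a visit.

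Loss unrelated to arm or recovery would cost only precision. Here it could be related to both. Only the experimental group is pressed to tingling pain (Experimental group, Control group), and whether flatus has been observed when a subject stops depends on how quickly that subject recovers.

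**Working it through.** **The two rules applied to one subject.** Take a subject treated at 6 h who refuses to continue at 18 h.
- Statistical analysis: treated at least once, so in the ITT set.
- Elimination criteria, item (2): removed from the study.
- If removal ends follow-up, the subject is in the ITT set without the outcomes still to come.
- If removal means exclusion from analysis, the subject is both in and out of the ITT set.

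The rules conflict on either reading.

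**The plan's own figure.** Inputs are from Sample size estimation: 1.96, 0.84, SDs 3.14 and 5.58, difference 4 h, dropout 15%.
- n = (1.96 + 0.84)² × (3.14² + 5.58²) / 4² = 7.84 × 40.996 / 16 = 20.09, rounded up to 21.
- 21 / 0.85 = 24.7, so 25 per group and 50 in total.

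This reproduces, and no sample size error is involved. The 15% allowance is 0.15 × 25 = 3.75 subjects per group (7.5 of 50) and covers dropout for every reason.

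**When refusal costs the primary outcome.** Inputs:
- Session times 6 + 12k h for k = 0 to 5, that is 6, 18, 30, 42, 54 and 66 h (Intervention).
- Preliminary times to flatus of 20.19 ± 3.14 (APP) and 30.82 ± 5.58 (sham) (Background). They are taken as hours because the target difference is in hours.

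Assumptions: normal distributions, and no allowance for the gap between end of surgery and return to the ward. The share without flatus at time t is 1 − Φ((t − mean)/SD). A second APP column uses a mean of 30.82 − 4 = 26.82, the difference the trial is sized for.

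| Time | APP, mean 20.19 | APP, mean 26.82 | Sham, mean 30.82 |
|---|---|---|---|
| 18 h | z = −0.70, 76% | z = −2.81, 99.8% | z = −2.30, 99% |
| 30 h | z = 3.12, 0.1% | z = 1.01, 16% | z = −0.15, 56% |
| 42 h | about 0% | about 0% | z = 2.00, 2.3% |
| 54 h, 66 h | about 0% | about 0% | about 0% |

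Removal at 18 h usually loses the primary outcome in both arms. Removal at 30 h loses it mainly in the sham arm. From 42 h on it almost never does.

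**Scale of a selective loss (illustration only).** If the slowest fraction q of an arm is removed, its observed mean falls by SD × φ(z₁₋q)/(1 − q).
- Sham: 0.9 h for q = 8% (2 of 25) and 1.6 h for q = 16% (4 of 25).
- APP: 0.5 h and 0.9 h for the same fractions.

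Loss in the sham arm shrinks the observed difference and loss in the APP arm enlarges it. These are worst cases set against a 4 h target, not predictions.

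**The case against.** The strongest reply is that the article never says recording stops. Items (6), inclusion by mistake, and (7), incomplete information, read like reasons to leave an evaluable set, and dropouts are to be described for each data set, so more than one set is foreseen. A condensed article may also leave the follow-up of discontinued subjects to a fuller document.

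Part of this stands. That recording stops is the natural reading of being removed from the study, but it is an inference, and silence on post-refusal assessment would not be a finding by itself. The point rests on two affirmative statements that cannot both be applied to the same subject, and reading removal as exclusion from analysis does not reconcile them.

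A reader might also infer more than the documents support:
- That the ITT analysis has no data for these subjects or cannot be carried out. Baseline and all evaluations before removal exist, and flatus is known for nearly all who stop from 42 h on.
- That declining a single session triggers removal. Item (2) speaks of refusing to continue the treatment. Item (7) might reach a skipped session, but only where efficacy and safety may have been affected.
- That the bias has a known direction. Tingling pain suggests more refusal in the APP arm, while the 30 h figures put more loss per refusal in the sham arm. No refusal rates are given, so the two cannot be combined.
- That 15% measures refusal. It covers all reasons and is already allowed for.

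**Conclusion.** The concern holds as a conflict between Elimination criteria and the ITT definition. With no provision for continued assessment, the ITT set will, on the natural reading, lack every outcome not yet observed at removal. For the primary outcome the exposure lies in refusals at about 18 h (76% APP and 99% sham still without flatus) and 30 h (0.1% to 16% APP, depending on whether the true difference is the preliminary 10.63 h or the planned 4 h, and 56% sham). It is close to nil from 42 h. Later 12-hourly scores, the discharge HADS and the post-discharge GIQLI are exposed whenever removal occurs before them, and a complete-case repeated-measures ANOVA would drop such subjects.

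The percentages rest on normality and on preliminary estimates; the SDs come from eight subjects according to Sample size estimation. The loss can differ by arm, but the direction and size of any bias cannot be stated.

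**What to change.** Reconcile Elimination criteria with Statistical analysis by separating two events: stopping study treatment, and withdrawing from the study.
- For subjects who stop or comply poorly with sessions, continue the recording already scheduled (flatus, defecation, 12-hourly evaluations, adverse events, HADS and GIQLI) unless consent to data collection is withdrawn, and keep them in the ITT analysis.
- Let a missed post-discharge visit affect only that visit's GIQLI value.
- Keep the per-protocol set as a separately defined set, so that non-compliance affects membership of that set and not data collection.

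This concerns recording and analysis only. It does not change when or why treatment is stopped.

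The cost is a rewording and one CRF field for treatment stopped, with date and reason. The ward evaluations and post-discharge GIQLI contacts are already scheduled, although the latter still require subjects to be reached after they leave hospital. The sample size stays at 50. Trial status says recruitment is ongoing, so the change should be made promptly: outcomes missed in the meantime cannot be recovered.
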